### Statistical analysis

The full analysis set (FAS) consists of all participants who received at least one injection. Participants will be analysed according to the group to which they were randomised. The per-protocol analysis set (PPS) is a subset of the FAS who have no major protocol violations. Participants presenting with at least one of the following protocol deviations will be excluded from the per protocol analysis: participant did not meet all protocol-specified inclusion criteria or met at least one of the protocol-specified exclusion criteria; participant did not complete the vaccination schedule; participant received a different vaccine than the one randomised to receive; participant did not receive vaccine within the protocol-determined time window; participant received additional seasonal trivalent influenza vaccines during the trial period; preparation and/or administration of the vaccine was not performed as per protocol.

The safety analysis set is defined as those participants who have received at least one vaccine. All participants will have their safety analysed according to the vaccine that they actually received. The FAS will be the primary analysis to infer superiority of a 180-day IIV3 booster vaccination compared to the active-comparator control in terms of the proportion of participants with day-208 HI antibody titres ≥1:40. This will be supported by per-protocol analysis. Analysis of secondary endpoints will use both the FAS and PPS.

Immunological data will be analysed per CHMP guidance (EMA/CHMP/VWP/457259/2014). Results will be presented by vaccine strain and will include GMTs (with 95% confidence intervals) and pre-/post-vaccination ratios (GMRs). Reverse cumulative distribution curves will also be provided, supplemented by tables presenting percentages of vaccinees with titres above a range of cut-off levels on a logarithmic scale.

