### Exclusion criteria

Participants meeting any of the exclusion criteria at baseline will be excluded from participation:Participation in the 4 weeks preceding the first trial vaccination or participation during the present trial period in another trial investigating a vaccine, drug, medical device, or medical procedureHistory of a life-threatening reaction to the vaccine used in the trial, or to a vaccine containing any of the same substancesKnown systemic hypersensitivity to any of the vaccine components, including:Egg protein (eggs or egg products)Chicken productsFormaldehydeNeomycin or kanamycinOctoxinol 9 (Triton X-100)Cetyltrimethylammonium bromide (CTAB)Thiomersal
History of Guillain-Barré syndrome (GBS) within 6 weeks following previous influenza vaccinationAcute respiratory infection (ARI) on the day of enrolmentModerate or severe acute illness/infection (according to investigator judgement) on the day of vaccination, or febrile illness (temperature ≥37.5 °C). A prospective participant should not be included in the study until the condition has resolved or the febrile event has subsidedSelf-reported thrombocytopenia, contraindicating intramuscular (IM) vaccinationKnown or suspected congenital or acquired immunodeficiency; or receipt of immunosuppressive therapy, such as anticancer chemotherapy or radiation therapy, within the preceding 6 months; or long-term systemic corticosteroid therapy (prednisolone ≥7.5 mg/day or equivalent for more than two consecutive weeks within the past 3 months)Chronic illness that, in the opinion of the investigator, is at a stage where it might interfere with trial conduct or completionDeprivation of freedom by an administrative or court order, or in an emergency setting, or hospitalised involuntarilyCurrent alcohol abuse or drug addiction that might interfere with the ability to comply with trial procedures in the opinion of the investigatorWomen of childbearing age will be excluded from the trial

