### Primary outcome

The primary outcome is the percentage of participants with seroprotection (HI titre ≥1:40) at day 208 post primary vaccination for each of the influenza strains present in the administered influenza vaccine.

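### The single per-protocol set excludes for an outside influenza vaccine taken at any time to day 360, so a vaccination after day 208 removes a day-208 titre it cannot have affected

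*Protocol article*

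**What the plan says.** All of the following is in the protocol article.

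- **One set, defined per participant** (Statistical analysis): "The per-protocol analysis set (PPS) is a subset of the FAS who have no major protocol violations". The consequence of a listed deviation is also fixed: "Participants presenting with at least one of the following protocol deviations will be excluded from the per protocol analysis".
- **The criterion at issue** (Statistical analysis): "participant received additional seasonal trivalent influenza vaccines during the trial period". No cut-off by visit is attached to it.
- **How the set is used** (Statistical analysis): the FAS carries the superiority inference on day-208 seroprotection. Of that analysis the article says "This will be supported by per-protocol analysis". It adds: "Analysis of secondary endpoints will use both the FAS and PPS".
- **When the primary outcome is measured** (Primary outcome): "The primary outcome is the percentage of participants with seroprotection (HI titre ≥1:40) at day 208 post primary vaccination".
- **How long the trial runs**: Summary of study design gives one year of follow-up with a last blood sample at day 360. Safety assessment methods names day 360 as the final visit. Treatment compliance and specific restrictions asks participants to avoid outside influenza vaccine for the whole study.
- **Event endpoints** (Secondary outcomes): influenza-like illness and PCR-confirmed influenza are counted by participant from day 208 to day 360.

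**The concern.** An analysis of a day-208 titre should not depend on what a participant does later. Under the stated rule it does: someone vaccinated elsewhere on, say, day 300 leaves the day-208 per-protocol comparison, although that vaccination cannot have changed the titre. The same person's PCR-confirmed influenza on, say, day 220 leaves the PPS event count as well.

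Two things are at stake, both within the PPS. Valid observations are lost, which costs precision. The set is also selected on an event after the outcome. If people who seek another vaccine differ in titre, or do so more often in one arm, the PPS difference moves for reasons unrelated to adherence up to day 208. The PPS is then a weaker check on the FAS result.

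Late vaccination is plausible on the article's own facts. From day 208 to day 360 is about five months. Trial materials allows that recommended strains may change while the trial runs, and the Discussion reports a change in at least one strain at 19 of 37 recommendations. The restriction on outside vaccine is a request to participants.

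**Working it through.** **1. Which listed deviations can first occur after day 208?** The list has six items. One concerns eligibility. Four concern the day-1 and day-180 injections: schedule not completed, wrong vaccine, outside the time window, and faulty preparation or administration. The sixth is the outside influenza vaccine, and it is the only one that clearly can arise first after day 208.

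**2. Reproducing the plan's sample size.** Inputs from Sample size calculation: control 60%, booster 80%, two-sided 5%, power 80%. Normal approximation with pooled variance under the null, mean rate 0.70:

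n per arm = [1.960 × √(2 × 0.70 × 0.30) + 0.842 × √(0.60 × 0.40 + 0.80 × 0.20)]² / 0.20²
= [1.2702 + 0.5323]² / 0.04 = 81.2, rounded up to **82 per arm, 164 in total**. This matches the article.

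**3. Power at a given n per arm.** Power = Φ[(0.20 × √n − 1.2702) / 0.6325].

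- n = 82: 80.4%.
- n = 85 (100 less the 15% dropout allowance): 81.8%.
- n = 90 (100 less the 10% loss also assumed in that section): 83.9%.

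**4. Non-selective loss from late vaccination.** The article gives no rate, so the shares below are assumptions.

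| Share vaccinated only after day 208 | From 85 per arm: n, power | From 90 per arm: n, power |
|---|---|---|
| 0% | 85.0, 81.8% | 90.0, 83.9% |
| 5% | 80.75, 79.8% | 85.5, 82.0% |
| 10% | 76.5, 77.6% | 81.0, 79.9% |
| 15% | 72.25, 75.2% | 76.5, 77.6% |

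With a day-208 set that counts only deviations up to that sample, the 0% row applies whatever the late uptake.

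**5. Selective loss.** If a share q of an arm with true rate p is removed, and a proportion r of those removed was seroprotected, the rate left is (p − q × r) / (1 − q). All values of q and r are assumed.

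- Both arms, q = 10%, r = 90%: control (60 − 9)/90 = 56.7%, booster (80 − 9)/90 = 78.9%. The difference is 22.2 points against a true 20.
- Control arm only, q = 10%:
  - r = 0%: control 60/90 = 66.7%, difference 13.3 points.
  - r = 30%: control (60 − 3)/90 = 63.3%, difference 16.7 points.
  - r = 60%: control (60 − 6)/90 = 60.0%, difference 20.0 points.

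So the shift can be upward, downward or nil.

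**The case against.** The strongest reply is that no primary inference rests on the PPS. The FAS takes everyone with at least one injection, analysed as randomised. It excludes nobody for an outside vaccine, and it keeps every late deviator's titre and influenza event, for secondary endpoints too. This stands, and it confines the point to the supportive and per-protocol secondary analyses.

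Late uptake may also be small. Participants are asked to avoid outside vaccine and are contacted every two weeks. Participants and study staff are blinded, which makes differential uptake less likely. That also stands. Blinding does not exclude differential uptake, because illness may prompt vaccination and illness may depend on titre. The figure of 82 per arm was set for the primary analysis, so a PPS below it breaches no target.

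For day-360 titres an exclusion period running to day 360 is appropriate, and a single set keeps one denominator. This is a fair argument for the rule at day 360. It does not justify applying the rule to day 208.

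A statistical analysis plan that is not shown could define visit-specific sets. The article, however, states the rule and its time span, so a visit-specific set would have to change this wording.

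A reader might infer more than the article supports:

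- **That joining another trial late is equally a PPS exclusion.** One exclusion criterion does mention "participation during the present trial period in another trial investigating a vaccine", but Exclusion criteria applies the whole list at baseline. The reading is arguable and is not relied on here.
- **That the PPS wrongly keeps people with a missing or mistimed day-208 sample.** Sample windows and evaluability are details that an article leaves to the full protocol or analysis plan.
- **That the day-208 result is delayed to day 360.** The article describes no earlier readout that could be delayed.

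**Conclusion.** The point holds for the outside-vaccine criterion. As written, a first outside influenza vaccination after day 208 removes an unaffected day-208 titre from the per-protocol analysis that supports the primary result, and removes earlier influenza events from the PPS secondary analyses.

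The non-selective effect is modest: from 85 per arm, power falls from 81.8% to 79.8%, 77.6% or 75.2% if 5%, 10% or 15% are affected. Selection could matter more, but its direction is not established. These figures rest on assumed rates of late vaccination and, for selection, on assumed titres among those removed.

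It would be wrong to infer that the primary result is biased or that influenza events are lost to the trial, because the FAS retains both. The article also does not show that the PPS difference would be inflated rather than diluted. The change is worth making because it costs almost nothing and the PPS is the named support for the primary conclusion.

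**What to change.** Define the PPS by time point in the Statistical analysis section, or in the analysis plan with the article's rule expressly replaced, before unblinding:

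- **Day-208 analysis:** only listed deviations occurring up to the day-208 sample exclude a participant.
- **Day-360 analysis:** only listed deviations occurring up to the day-360 sample exclude a participant.
- **Influenza events in the PPS:** do not discard an event that occurred before the deviation. How to treat follow-up after the deviation needs a stated choice. The endpoints are counts of participants, and censoring at the deviation would change that measure and could be informative if illness prompts vaccination.

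The cost is a few lines of text, with no new data or participants; the date of any outside vaccination must be available. The downside is that PPS denominators will differ between visits and must be reported with each result.

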**Methods/design:**

This is a single-centre, randomised, observer-blind, active-comparator controlled, parallel-group, phase IV trial in 200 adults aged 65 years or older. Study participants will be assigned to one of two groups in a 1:1 ratio and followed for 1 year, with five scheduled visits. The control group will receive IIV3 at day 1, and an active comparator (Tetanus-diphtheria-pertussis vaccine) at day 180. Participants in the experimental group will receive IIV3 containing the same strains at day 1 and day 180. Endpoints are immunological, and include measures of HI titres, microneutralisation titres (MN) and cell-mediated immunity from first vaccination up to day 360.

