**Fig. 2 Fig2:**

Study timeline from day 1 (D1) to day 360 (D360)

Solicited and unsolicited adverse events (AEs) will be collected for all participants for 7 days after each vaccination. All serious adverse events (SAEs) will be collected for 28 days after each vaccination. SAEs that are considered related to vaccination and/or study procedures will be monitored until resolution or stable. Participants will also be contacted 2-weekly as surveillance for clinical endpoints, including influenza-like illnesses (ILI) and polymerase chain reaction (PCR)-confirmed influenza.

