### Potential risks

As with any vaccination, participants may experience pain, swelling, redness or itching at the injection site. Rarely, a participant may experience an allergic reaction which produces rash, urticaria or difficulty breathing. Serious allergic reactions that can be life-threatening may occur. The incidence of severe adverse reactions are low with the trial vaccines. An increased risk of SAEs has not been reported from studies of repeated vaccination at 1 year or earlier. The risk of nonsevere local and systemic adverse reactions may be increased with repeated vaccination as a result of increased reactogenicity from pre-existing immunity. Blood taking is a common medical procedure with very low risk of complications, such as prolonged bleeding or infection, when standard procedures are followed. Risks of breaches in trial participant confidentiality will be ameliorated by following the Singapore Guideline for Good Clinical Practice (SGGCP) and the DSRB-approved study protocol.

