## Discussion

This clinical trial addresses a neglected issue in tropical countries. Demonstrating superior protection against influenza infection with a simple booster vaccination has the potential to offer a significant public health benefit. For example, in South East Asia alone, demographic estimates by the United Nations are for the number of persons aged 65 years and older to almost triple over the next 30 years, from 37.6 million in 2015, to 111.3 million in 2045 [14].

A 6-monthly booster schedule with standard dose inactivated trivalent vaccine is attractive due to its simplicity, low cost, and safety profile. This would support its implementation into clinical practice if proven to offer superior efficacy against influenza infection. Six-monthly vaccination coincides with the approximate periodicity of epidemics in countries with biannual seasons synchronous with the Northern and Southern Hemisphere winters. A 6-monthly schedule also coincides with WHO strain recommendations which, since 1999, have been made biannually [15]. Between hemisphere winters, a change in at least one of the strains in the trivalent vaccine has been recommended approximately half of the time (19/37 from 1999 till the SH 2017 recommendations). Repeat vaccinations are not associated with an increased risk of AEs, though data is not available for 6-monthly vaccination [16].

The limitations in older people of standard dose inactivated influenza vaccine are well understood [17]. Even if this study finds a significant immunological benefit from repeat vaccination at 6 months, this may not be the optimal solution for providing year-round protection. Alternative influenza vaccine formulations have been licensed for older people; for example, a high-dose vaccine with 60 μg of haemagglutinin (HA) per strain, and vaccines which include an immune adjuvant. These vaccines do offer superior short-term immunogenicity in older people, which in some studies persists for at least 6 months [18–20]. However, by 1 year, either no significant residual benefit is reported (adjuvanted vaccine), or data is not currently available (high-dose vaccine) [21, 22].

If evidence of significantly improved seroprotection by an IIV3 booster can be inferred from this study, we believe that it will provide the basis for a large-scale clinical trial in older people to determine whether this translates into reduced influenza infection rates.

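### The SAE outcome counts events from day 1 to day 360, although the safety objective is the day-180 booster and the arms are treated alike until then

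*Protocol article*

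**What the plan says.** All references are to the protocol article.

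- **Objective.** Secondary objectives include assessing the safety of an IIV3 booster at 180 days.
- **Treatment.** "The control group will receive IIV3 at day 1, and an active comparator (Tetanus-diphtheria-pertussis vaccine) at day 180" (Abstract, Methods/design). The other arm is given IIV3, with unchanged strains, on both occasions.
- **SAE outcome.** Secondary outcomes lists the percentage of participants with an SAE over day 1 to day 360. In the same list, healthcare use and all-cause mortality are compared across groups from day 180 to day 360.
- **Analysis set and grouping.** One vaccination is enough to enter the safety set. The grouping rule then reads: "All participants will have their safety analysed according to the vaccine that they actually received" (Statistical analysis).
- **Reactions.** Under Fig. 2: "Solicited and unsolicited adverse events (AEs) will be collected for all participants for 7 days after each vaccination".
- **Prior view of the hazard.** Potential risks has this sentence: "The risk of nonsevere local and systemic adverse reactions may be increased with repeated vaccination as a result of increased reactogenicity from pre-existing immunity". The Discussion takes another line: "Repeat vaccinations are not associated with an increased risk of AEs, though data is not available for 6-monthly vaccination".

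**The concern.** The safety question is what a second IIV3 dose at day 180 adds. Until that injection the two arms have had the same single dose of the same product, so any SAE between day 1 and day 180 says nothing about the booster. The SAE outcome nevertheless counts those events, although two neighbouring outcomes in the same list start at day 180.

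The grouping rule does not help. A participant who leaves before day 180 has received one IIV3 dose whichever arm he or she was in, so vaccine received cannot place that person on either side of the comparison. Such a person is still in the safety set, which requires only one vaccination.

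At stake is how informative the trial's SAE comparison is for a schedule on which, by the article's own account, no data exist. A contrast diluted by pre-booster events can look more reassuring than it should.

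**Working it through.** **What the article gives.** It states no SAE rate and no power for safety, so there is no safety figure to reproduce. Its only sample-size figure is for seroprotection: 60% against 80%, two-sided 5%, 80% power. The pooled normal approximation gives 82 per group, 164 in total, as stated. The planned enrolment of 100 per group is used below. All SAE rates are assumptions.

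**Step 1: effect of the window.** Assume risk *r* in each half-year, independent between halves, doubled in the second half in the booster arm, with no dropout.

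- Day 180 to 360, *r* = 5%: control 5%, booster 10%. Ratio 2.0, difference 5.0 points.
- Day 1 to 360: control 1 − 0.95 × 0.95 = 9.75%; booster 1 − 0.95 × 0.90 = 14.5%. Ratio 14.5/9.75 = 1.49, difference 4.75 points.

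In general the full-window ratio is (3 − 2*r*)/(2 − *r*) and the difference is *r*(1 − *r*):

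| *r* | Ratio, day 180–360 | Ratio, day 1–360 | Difference, day 180–360 | Difference, day 1–360 |
|---|---|---|---|---|
| 2% | 2.0 | 2.96/1.98 = 1.49 | 2.0 points | 1.96 points |
| 5% | 2.0 | 2.90/1.95 = 1.49 | 5.0 points | 4.75 points |
| 10% | 2.0 | 2.80/1.90 = 1.47 | 10.0 points | 9.0 points |

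A doubling appears as about 1.5 whatever the background rate. The difference shrinks little.

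**Step 2: noise.** Standard error of the difference at *r* = 5%:

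- Day 180 to 360, 100 per arm: √[(0.05 × 0.95 + 0.10 × 0.90)/100] = 3.7 points; difference/SE = 5.0/3.7 = 1.35.
- Day 1 to 360, 100 per arm: √[(0.0975 × 0.9025 + 0.145 × 0.855)/100] = 4.6 points; difference/SE = 4.75/4.6 = 1.03.
- Day 180 to 360 with only 85 per arm (the 15% dropout allowed for): √(0.1375/85) = 4.0 points; difference/SE = 1.24, still above 1.03.

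**Step 3: power under a second set of assumptions.** Constant background risk *b* per 28 days, plus an independent 10% risk from the booster; 100 per arm, two-sided 5%. Over *k* periods of 28 days, control is 1 − (1 − *b*)^*k* and booster is 1 − (1 − *b*)^*k* × 0.90.

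| *b* | 28 days after booster | Day 180–360 | Day 1–360 |
|---|---|---|---|
| 1% | 1.0% vs 10.9%: 85% | 6.3% vs 15.6%: 57% | 12.1% vs 20.9%: 39% |
| 2% | 2.0% vs 11.8%: 78% | 12.2% vs 21.0%: 39% | 22.9% vs 30.6%: 23% |

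With a 5% booster risk, power over day 180–360 and day 1–360 is 22% and 14% (*b* = 1%), or 14% and 9% (*b* = 2%). The trial is small for SAEs in any window; starting at day 1 makes this worse.

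**Step 4: can second-dose reactions be seen?** Reactions are recorded after each vaccination, so dose 2 can be set against dose 1. At assumed rates, 100 per dose and treating doses as unpaired, power is 88% for 20% against 40%, 66% for 20% against 35%, and 37% for 20% against 30%. Moderate to large excesses are detectable; small ones would often be missed.

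**The case against.** The strongest reply is that the SAE item is a whole-trial description. It is worded as a percentage, without the across-groups phrase used for mortality and healthcare use. Death and hospitalisation are SAE criteria and are already compared from day 180. The article does not expect vaccine-related SAEs in a trial of this size, the rates above are invented, and the absolute excess hardly moves.

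Much of this stands. The size is hypothetical, the absolute excess is nearly preserved, and nothing prevents a split at day 180. But if the item is only descriptive, the booster objective has no outcome for SAEs as a whole in the period after the booster. Deaths and hospitalisations do not fill that gap: the SAE definition also covers life-threatening events, lasting disability and medically important events.

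A reader might infer something stronger: that safety is analysed by vaccine instead of by dose, so that about 200 first and 100 second IIV3 doses are pooled and a rise in reactions which the plan expects cannot be seen. The article does not support this.

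- The sentence "All participants will have their safety analysed according to the vaccine that they actually received" follows the definition of the safety set and parallels the as-randomised rule for the full analysis set. It neither states pooling nor excludes tables by dose, which are commonly left to an analysis plan.
- Reactions are collected after each injection, so the data exist (Step 4).
- Potential risks says only that nonsevere reactions "may be increased with repeated vaccination as a result of increased reactogenicity from pre-existing immunity", which is a possibility, and the Discussion says the opposite.
- The SAE window has no bearing on that hazard, which concerns nonsevere reactions recorded in the 7-day diary.

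**Conclusion.** The point holds for the SAE outcome. Its window of day 1 to day 360 does not match the booster-safety objective, because roughly half of it precedes any difference between the arms. Under the assumption of equal half-year risks doubled by the booster, a ratio of 2.0 appears as about 1.5 for background risks of 2% to 10%. The absolute excess falls only slightly (5.0 to 4.75 points at 5%) but its standard error rises from 3.7 to 4.6 points. Under the alternative assumptions with a 10% booster risk, power falls from 57% to 39% or from 39% to 23%. None of these rates comes from the article. The primary outcome is not affected.

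Reporting reactions by dose is a clarification, not an error in the plan. It is useful because the concurrent day-180 contrast is with TDap, itself an active vaccine, and so does not isolate the added reactogenicity of a second IIV3 dose. The statements in Potential risks and the Discussion pull in opposite directions and need reconciling.

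**What to change.** 1. In Secondary outcomes, make the between-group SAE comparison on events with onset from the day-180 injection to day 360, among participants given that injection and grouped by what they received then. This matches the mortality and healthcare-use window. Because participants and investigators are blinded from day 1, restricting to those who reach the injection should not by itself favour an arm; report the numbers lost before day 180 by arm.
2. Report SAEs from day 1 up to the day-180 injection descriptively, both arms pooled.
3. As a clarification, report solicited and unsolicited adverse events by dose (IIV3 dose 1, IIV3 dose 2, TDap), and dose 2 against dose 1 within the experimental arm.
4. Reconcile the statements on repeat vaccination in Potential risks and the Discussion.

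Item 1 relies on SAE collection to day 360, as Safety assessment methods states. The text under Fig. 2 and the Safety monitoring plan give 28 days after each vaccination, so those passages must also be reconciled.

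If collection runs to day 360, the cost is some wording, one extra SAE table and adverse-event tables laid out by dose, with no new data. The change should be made before unblinding, so that the safety comparison is not chosen after results are seen.

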As an alternative to clinical effectiveness, the trajectory of immune responses after vaccination can be used to estimate the duration of protection. The haemagglutination inhibition (HI) titre is the major immune correlate of protection, and is used by regulatory agencies, such as the Food and Drug Administration (FDA) and the European Medicines Agency (EMA), for influenza vaccine licensing. A titre ≥1:40 is estimated to offer 50% protection against infection, and this threshold is conventionally labelled as ‘seroprotection’ [9]. A systematic review of vaccine antibody persistence studies, performed by the study team in preparation for this trial, suggested that in older people there is a steady decline in HI titres, and at between 180 and 360 days titres return to the pre-vaccination level [10]. Studies have identified increasing age and lower pre-existing HI titres as predicting reduced duration of antibody persistence, while the impact of comorbidities, such as diabetes, on persistence is less clear [11, 12].

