## Methods/design

### Summary of study design

This is a single-centre, randomised, observer-blind, active-comparator controlled, parallel-group, phase IV trial in 200 adults aged 65 years or older. Each study participant who meets eligibility criteria and signs the Informed Consent Form will be allocated to one of two groups in a 1:1 ratio (Fig. 1). Participants will be followed for 1 year, with five scheduled visits. All participants will provide blood samples for immunogenicity assessment at days 1 (pre-injection), 28, 180 (pre-injection), 208, and 360 (Fig. 2).

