### Randomisation

A web-based, computer-generated randomisation code will assign participants using a random permuted block method. Allocation will be stratified by age (65 years or under to 74 years, 75 years or older). Age is a significant predictor of response to vaccination, and the proportion of participants recruited who are older than 75 years may be small.

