### Sample size calculation

The following assumptions were made for determination of sample size expected to meet primary outcome:Rate of seroprotection (HI antibody titre ≥1:40) on day 208 after vaccination is 60%Proportion seroprotected at day 208 in the experimental group will be 80%A loss to follow-up rate of 10%A power (1 − *β*) of 80% to detect differences between the two primary study groupsA two-sided significance level (*α*) of 5%

The primary statistical null hypothesis is of no increase in seroprotection rates (HI antibody titre ≥1:40) at day 208 following booster IIV3 vaccination, compared to a control injection. Formally, the trial will test:H_0_: Seroprotection rate (booster) = seroprotection rate (control), versusH_A_: Seroprotection rate (booster) ≠ seroprotection rate (control)

A sample size of 164 (82 per group) will provide 80% power to test this hypothesis, based on approximations to the normal distribution. A total sample size of 200 (100 per group) has been chosen to allow for up to 15% dropout. This sample size will provide adequate power for a range of seroprotection rates assuming an increase in absolute seroprotection of at least 20%.

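### The primary comparison is framed and sized on unadjusted rates; prespecifying adjustment for the day-180 pre-injection titre would be a cheap gain in efficiency, of a size the article does not let us fix

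*Protocol article*

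**What the plan says.** - **Primary analysis** (Protocol article, Statistical analysis). Superiority is inferred in the full analysis set "in terms of the proportion of participants with day-208 HI antibody titres ≥1:40", supported by the per-protocol set. No test, model, effect measure or covariate is named.
- **Hypothesis and size** (Sample size calculation). The null hypothesis is equality of the two seroprotection rates. The inputs are "Rate of seroprotection (HI antibody titre ≥1:40) on day 208 after vaccination is 60" per cent and "Proportion seroprotected at day 208 in the experimental group will be 80" per cent. They give 82 per group for 80% power at two-sided 5% by a normal approximation. The total is 200, to allow up to 15% dropout.
- **Stratification** (Randomisation). Allocation is stratified by age in two bands, because "Age is a significant predictor of response to vaccination".
- **Prognostic factors** (Background). Earlier studies are said to identify "increasing age and lower pre-existing HI titres as predicting reduced duration of antibody persistence".
- **Sampling** (Summary of study design). "All participants will provide blood samples for immunogenicity assessment at days 1 (pre-injection), 28, 180 (pre-injection), 208, and 360".
- **Secondary titre outcomes** (Secondary outcomes). The geometric mean ratio and seroconversion from day 208 to day 360 are both defined against the day-1 titre.

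**The concern.** The two arms receive the same influenza vaccine at day 1 and diverge only at the day-180 injection. A titre drawn at day 180 before that injection therefore cannot be affected by the randomised difference, and for the booster question it is the natural baseline. In the control arm it is also the same assay read 28 days before the primary endpoint, with no influenza vaccine in between, so a useful correlation with the day-208 titre is plausible.

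The article collects this measurement on everyone but gives it no role in the comparison between arms. The primary comparison is set up on two raw rates. The post-booster ratio uses a baseline about seven months before the day-208 sample, so it combines the primary response, its waning and the booster effect.

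What is at stake is precision. The primary outcome is read for each of three strains, each with power not far above 80% once dropout is allowed for. The sample is fixed and withdrawn participants are not replaced.

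**Working it through.** **1. Reproduce the plan's figure.** Inputs from Sample size calculation: control 0.60, booster 0.80, mean 0.70, two-sided 5%, power 80%. Pooled normal approximation:

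n = [1.96·√(2·0.70·0.30) + 0.8416·√(0.60·0.40 + 0.80·0.20)]² / 0.20²
= [1.2702 + 0.5323]² / 0.04 = 81.2, so 82 per group.

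This matches the article with no covariate in the formula. Power is 80.4% at 82 per group, 81.8% at 85 (100 × 0.85) and 87.6% at 100. The design meets its own target.

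**2. Age stratum alone.** The article gives neither an age effect nor the size of the older stratum. Assume 20% are aged 75 or older. If the strata differ by δ in seroprotection in both arms, the share of variance explained is 2·0.2·0.8·δ² / (0.24 + 0.16):

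- δ = 0.10: 0.0032/0.40 = 0.8%
- δ = 0.20: 0.0128/0.40 = 3.2%
- δ = 0.30: 0.0288/0.40 = 7.2%

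In simulation with the strata balanced across arms, as stratified allocation intends, the variance of the estimate did not change. Power moved by about 1 point at most (for example 80.4% to 81.5% with a 0.6 SD age shift).

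**3. Adding the day-180 titre.** The day-180/day-208 correlation is not in the article, so a range is assumed on the latent log-titre scale, as control/booster. The unadjusted two-proportion test is compared with a standardised risk difference from arm-specific logistic models containing age stratum and day-180 log titre, with an influence-function standard error. Simulation at 82 per group, 2,000 trials per row, age shift 0.3 SD:

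| Assumed correlation | Power, unadjusted | Power, adjusted | Variance ratio |
|---|---|---|---|
| 0 / 0 | 78.7% | 79.4% | 1.00 |
| 0.5 / 0.3 | 79.6% | 84.7% | 0.90 |
| 0.7 / 0.5 | 81.5% | 89.5% | 0.80 |
| 0.9 / 0.5 | 78.8% | 92.5% | 0.69 |
| 0.9 / 0.7 | 80.2% | 96.4% | 0.58 |

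The Monte Carlo standard error of one power figure is about √(0.8·0.2/2000) = 0.9 points.

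At 85 per group, the number left after 15% dropout, gains over about 82% are roughly 0, 1, 4, 9 and 16 points at 0/0, 0.3/0.1, 0.5/0.3, 0.7/0.5 and 0.9/0.7.

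**4. Type I error.** With both rates at 60% and a correlation of 0.9 in both arms, rejection was 5.2% adjusted and 4.4% unadjusted. Both are close to nominal.

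**5. Log titres.** For a continuous titre, ANCOVA on a baseline with correlation r leaves a fraction 1 − r² of the variance. At an assumed r = 0.7 that is 1 − 0.49 = 0.51, a 49% cut.

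**The case against.** The strongest reply is that the article does not say the primary analysis is unadjusted. It names an endpoint and analysis sets and defers to regulatory guidance. A covariate list is commonly left to the full protocol or analysis plan, neither of which is shown, and a sizing formula without covariates does not bind the analysis. This stands: a reader might infer that the plan rules out or deliberately ignores adjustment, and the text does not support that. What remains is that the hypothesis, the sizing and the day-1 baseline are explicit, and a better-suited baseline is already collected.

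Other stronger readings also fail:

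- **That the analysis is invalid or the trial underpowered.** The unadjusted test holds its error rate and reaches the stated 80%. Any shortfall in winning on all three strains is a separate multiplicity question.
- **That leaving out the age stratum costs real precision.** It costs about a point of power or less, and the article itself expects the older group may be small.
- **That the gain is known to be large.** The Background sentence concerns how long antibody persists, not the response 28 days after a booster. If the booster lifts most people past 1:40 whatever their earlier titre, the gain is small.
- **That the day-1 ratio is wrong.** It is a legitimate fold-rise summary and a secondary outcome. It is just a weak basis for comparing arms after the booster.
- **That adjustment is free.** Missing day-180 titres need a rule, and the estimator must be fixed in advance for each strain.

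**Conclusion.** The point holds as an efficiency recommendation. The article frames and sizes the primary comparison on two unadjusted rates and uses day 1 as the baseline for the post-booster ratio, although a valid covariate measured just before the arms diverge is drawn from everyone.

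At 85 per group the benefit of using it runs from nothing to about 16 power points, entirely according to a correlation the article does not give. With moderate to high correlation (0.7/0.5 upward, at 82 per group) the variance falls by 20% to 42%. At zero correlation nothing material is lost. These figures also assume 60% and 80% seroprotection, a normal latent log titre and 20% of participants aged 75 or older. Nearly all the gain comes from the titre, not the age stratum.

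**What to change.** In Statistical analysis, prespecify before unblinding, separately for each strain:

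- **Primary estimate:** a standardised (marginal) risk difference for day-208 seroprotection, from a logistic model with arm, age stratum (under 75, 75 or older) and log2 day-180 pre-injection titre, with a robust 95% confidence interval. Standardising keeps the estimand as the difference in rates on which the trial was sized; a conditional odds ratio would answer a different question.
- **Titres:** ANCOVA of log titres at days 208 and 360 with the same covariates.
- **Missing day-180 titres:** a stated rule, needed because the full analysis set includes anyone given one injection.
- **Descriptive tables:** keep the raw proportions, geometric mean titres and day-1 ratios as planned.

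The cost is some wording and a few lines of code. No new data, visits or change in sample size are needed.
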